## Participant Enrolment and Follow-Up

This study will enrol 2792 pregnant women over a period of 18-24 months. Enrolment and follow up will occur through Hospital and Health Centre Antenatal Clinics. Apart from some ultrasound visits (particularly at enrolment), no additional study visits will be required, beyond visits for standard antenatal care.

Currently there are high levels of ANC attendance in Madang. If women miss a treatment or follow-up visit they will be visited on the next day by a village reporter and encouraged to visit the health centre or the hospital ANC. We therefore expect >90% attendance at any follow-up time point.

However, people in the study areas do occasionally move the village of residence. In addition some people do grow tired of participating in intensive longitudinal follow up studies and withdraw consent for continued participation.

Women that missed more than 2 treatments will be excluded from all analyses except those on drug side effects. Consequently, we expect about 20% loss of follow-up.

## Analysis Plan

### Primary Outcome Measures

The analyses for the primary outcome measures will use logistic regression. The primary outcome will be defined as number women giving birth to a child with a birth weight of <2500g. These analyses will adjusted for different covariates such as sex, gestation, genotype, bed net use, number of IPTp treatments received, season of delivery (wet vs dry) and site.

Differences in birth weight will be assessed using analyses of variance (ANOVA) and adjusted for the same covariates.

### Secondary Outcome Measures

Logistic regression will also be used to analyses parasite prevalence at delivery (for all 4 Plasmodium species individually as well as combined) and prevalence of STIs at 2nd/final treatment time point. Mean haemoglobin levels will be compared using ANOVA.

Statistical analyses will be done using STATA, SPLUS and SAS statistical software.

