## Randomisation and Blinding

### Randomisation procedures

Women will be randomized to receive SP/AZ or SP/CQ using concealed allocation. Each treatment will be randomly assigned to 4 different treatment codes, resulting in a total of 8 treatment codes (i.e. A, B, C, D, E, F, G, H). A block randomization procedure will be used, with blocks of 32, each containing 4 women assigned to each treatment code. This will help maintain concealment of allocation from study staff to the greatest extent possible.

In order to facilitate field operations independent randomization lists will be produced for each health centre / hospital. The resulting list will contain 1500 women for Modilon Hospital, 500 for each of the peripheral clinics in Madang Town, 500 each for the two field teams operating in the Madang North Coast (Mugil & Alexishafen HC) and 500 for Yagaum Health Centre. .

The lists will be generated by an independent statistician, and the code will be held by the DSMB.

Administration of second and third treatment doses will be placebo controlled.

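### Site is a randomisation stratum and a covariate in the birth-weight models, but the secondary analyses name no site term; if outcomes differ by site, the tests as written are mildly conservative.

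*Combined protocol and SAP*

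**What the plan says.** - **Allocation (6.3.1).** To ease field work, "independent randomization lists will be produced for each health centre / hospital". Within each list, "A block randomization procedure will be used, with blocks of 32, each containing 4 women assigned to each treatment code". Four codes belong to each treatment, so a block holds 16 women per arm. On list sizes: "The resulting list will contain 1500 women for Modilon Hospital, 500 for each of the peripheral clinics in Madang Town", with 500 for each of the two North Coast teams and 500 for Yagaum. Site is therefore a randomisation stratum with seven levels.
- **Birth-weight outcomes (11.4.1).** The covariates listed for the low birth weight model end with "number of IPTp treatments received, season of delivery (wet vs dry) and site". For mean birth weight: "Differences in birth weight will be assessed using analyses of variance (ANOVA) and adjusted for the same covariates".
- **Secondary outcomes (11.4.2).** "Logistic regression will also be used to analyses parasite prevalence at delivery", and the same sentence covers STI prevalence. For haemoglobin: "Mean haemoglobin levels will be compared using ANOVA". The section names no covariate or stratum and does not refer back to the list in 11.4.1. Nothing elsewhere adds site to these models.

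**The concern.** Blocking within site balances the arms at each site, so differences between sites largely cancel out of the arm comparison. A model without site still counts those differences as residual noise. Its standard error is then larger than the true sampling variability of its estimate, the test rejects less often than its nominal 5% under the null, and some power is lost.

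Site differences are plausible. The sites are a provincial hospital, town clinics and health centres outside the town, and malaria and STI prevalence could vary among them. At stake are a small loss of power on the secondary outcomes and results reported on a different footing from the birth-weight outcomes. There is also an analysis choice left open until data are in hand.

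**Working it through.** **Inputs from the documents.** Seven site lists, 1500 for the hospital and 500 for each of the six others; blocks of 32, 1:1 (6.3.1). Two-sided 5% tests with 80% power; haemoglobin 10.0 vs 10.3 g/dl, 845 per arm; *P. falciparum* 30% vs 20%, 389 per arm; STI 30% vs 10%, 72 per arm (11.2, Table 3).

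**Assumed.** The share ρ of outcome variance that lies between sites. The documents give none.

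**The plan's own figures.**
- Haemoglobin: n = 2·SD²·(1.96 + 0.84)²/0.3². No SD is stated; 845 implies SD = 2.2. Cross-check: at 1163 per arm the detectable difference is 2.80 × 2.2 × √(2/1163) = 0.256, which agrees with the 0.26 g/dl stated in 11.2.
- *P. falciparum*: two Poisson rates give (1.96 + 0.84)² × (0.30 + 0.20)/0.10² = 392, close to the stated 389.
- STI: two proportions with continuity correction give 72, as stated.

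This point disputes none of these.

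**Formula.** With balance within site, the true variance of the arm difference contains only the within-site part, (1 − ρ) of the total. The unadjusted model uses the total. Hence:
- model SE / true SD = 1/√(1 − ρ)
- true two-sided error = 2·[1 − Φ(1.96/√(1 − ρ))]

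**Haemoglobin.** The power and sample-size columns use SD = 2.2·√(1 − ρ). The last two columns come from 2000 simulated trials per row, with blocks of 32 within seven sites weighted by list size and about 2326 women (2 × 1163).

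| ρ | SE ratio without site | Power at 845, site included | n per arm for 80%, site included | Simulated ratio, without site | Simulated ratio, with site |
|---|---|---|---|---|---|
| 0 | 1.000 | 80.0% | 845 | 1.01 | 1.01 |
| 0.01 | 1.005 | 80.4% | 836 | 1.01 | 1.00 |
| 0.02 | 1.010 | 80.8% | 828 | 1.01 | 1.00 |
| 0.05 | 1.026 | 82.0% | 802 | 1.04 | 1.01 |
| 0.10 | 1.054 | 84.0% | 760 | 1.06 | 1.00 |

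Simulation error on these ratios is about 1/√(2 × 2000) = 1.6%, so the simulation agrees with the formula. At ρ = 0.10 the simulated two-sided error was 3.5% without site and 4.5% with it. The formula gives 3.9% without site, and simulation error here is about 0.5 points.

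**Binary outcome, *P. falciparum* averaging 30%.** Take seven equal sites with evenly spaced prevalence. Then ρ = var(site prevalence)/(0.30 × 0.70), using the population variance.
- Sites from 15% to 45%: variance 0.0100; ρ = 0.0100/0.21 = 4.8%; true error about 4.5%.
- Sites from 10% to 50%: variance 0.0178; ρ = 0.0178/0.21 = 8.5%; true error about 4.1%.

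Equal sites is a simplification. With the list-size weights, ρ is about 3.7% and 6.6% if the hospital sits mid-range, and up to about 6.0% and 10.9% if it sits at an extreme.

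**Logistic models, 30% vs 20%, simulated (1500 trials per row).**
- Without site, model SE / true SD was 1.01, 1.02, 1.02 and 1.06 at ρ = 0.009, 0.034, 0.076 and 0.129.
- At ρ = 0.129, adding site raised the SE from 0.0941 to 0.1007 and moved the log odds ratio from −0.474 to −0.540. The test statistic goes from 0.474/0.0941 = 5.0 to 0.540/0.1007 = 5.4.

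**The case against.** The strongest reply has three parts.

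**The text is silent and does not exclude site.** Section 11.4.2 follows directly from 11.4.1, says logistic regression will *also* be used, and rules nothing out. The covariates in 11.4.1 are themselves given as examples. A reader might infer that the plan deliberately leaves site out; the documents do not say so. What stands is narrower. Section 11.4.1 takes the trouble to carry the covariates over to birth weight, and 11.4.2 does not do so for any outcome. The word *also* carries over the method and not the list.

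**The effect is conditional and small.** A reader might infer that the secondary standard errors are certainly too wide. That holds only where the outcome differs by site, which the documents do not quantify; with no site variation nothing changes. There is also room to spare. With 1163 evaluable per arm and the back-solved SD of 2.2, haemoglobin power is already about 91%. For *P. falciparum*, power is about 99% even at 698 per arm (60% of 1163, borrowing the placental-specimen rate in 11.2). This stands, and it limits the weight of the point.

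**Logistic regression behaves differently.** A reader might infer that leaving site out biases the odds ratio, or that adding it would narrow the interval. Neither is right. The unadjusted odds ratio estimates a marginal quantity and the adjusted one a within-site quantity, so they are different estimands. The standard error rises on adjustment, as the figures above show.

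One consideration runs the other way. Secondary outcomes are analysed only in women with a usable sample (11.1.3), so balance within site is not guaranteed in those subsets. A site term would also deal with any site imbalance that arises there.

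**Conclusion.** The point holds as a minor one. Site defines the randomisation strata and is in the birth-weight models, but the analyses of parasite prevalence, STI prevalence and haemoglobin are stated without it. Followed as written, they are calibrated only if outcomes do not differ by site, and are otherwise slightly conservative.

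The size rests on the assumed site share. For shares of 0 to 10%, the haemoglobin standard error is about 0 to 5% too wide, and at most about four percentage points of power are forgone at 845 per arm (using the back-solved SD of 2.2). For *P. falciparum* under the two assumed spreads, the true two-sided error is about 4.5% or 4.1%. The gain from adjusting the logistic models is correct calibration and a slightly larger test statistic, not a narrower interval.

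The documents do not support a reading in which false-positive findings become more likely, the primary outcome is affected, or a stated sample size is wrong.

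**What to change.** In 11.4.2, state that every between-arm secondary comparison (parasite prevalence by species and combined, STI prevalence, and haemoglobin) includes the randomising site as a fixed factor, or is Mantel-Haenszel stratified by site. State also that this estimate is the main secondary result, and that adjusted odds ratios are within-site odds ratios.

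The cost is one sentence and about six degrees of freedom (seven sites). Site is already a covariate in 11.4.1, so no new data are needed and no sample size changes.

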**Tools to control malaria in pregnancy**

Presently we have two principal tools to control malaria in pregnancy, and to reduce related mortality: insecticide-treated materials, and antimalarial drugs, given as regular prophylaxis or as intermittent preventive treatment for pregnancy (IPTp). PNG is now supplying long-lasting ITNs to all malaria-exposed individuals through the Global Fund; given the very high levels of chloroquine resistance and poor compliance of women with weekly CQ, ITNs are now seen as a preferred alternative to chloroquine prophylaxis. IPTp involves the regular administration of treatment doses of an appropriate antimalarial agent, at 2 or more time points during pregnancy (WHO Draft Strategic Framework). The leading candidate for IPTp in Africa is sulfadoxine-pyrimethamine (SP). In several studies, SP in two or more doses decreased malaria prevalence in peripheral and placental blood and reduces maternal anaemia and improves birth weight 6-10. The risk of malaria is highest in first pregnancy, and some suggest limiting prophylaxis to this group. However, drugs that effectively prevent malaria may also restrict the development of immunity to pregnancy malaria, placing women in later pregnancies at risk of disease. The interplay between drug control of disease and immune response is presently poorly understood. There is presently no information on the impact of IPTp on *P vivax* in pregnancy. If vivax infection causes significant morbidity, choice of antimalarials will need to be guided both by drug sensitivity of *P falciparum* and by *P vivax* sensitivity.

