# Study Population

## Selection of the Study Population

In order to be able to enrol 2792 pregnant women in 18 months (and to limit numbers of multigravid women to equivalence with primigravid women) we will need to recruit women at multiple sites. The studies will therefore be conducted at several Health Centres and the Provincial Hospital in Madang Province.

Modilon Hospital has approximately 1100 ANC bookings, and >1500 deliveries, each year. Clinics in Madang town see around 700 new patients each year. Mugil and Alexishafen Health Centres each have 500-600 ANC bookings, and Yagaum Health Centre has 250 deliveries annually. Average parity is approximately 5; we estimate that 50% of ANC attendees will be multigravidae and 20% primigravidae, and therefore about 70% of women will be eligible for the study. Of >4000 potential enrolees, we plan to enrol approximately 65%.

Women are eligible for participation in this study if they fulfil the following criteria:

- - permanent resident in study area
  - exclusive use of study health facilities for primary health care
  - primigravid, secundigravid, or multigravid women; the latter will be enrolled in a 1:1 ratio with primigravid women.
  - Age is between 16 and 49 years

For studies of the effects of pregnancy on P viva immunity, we will re-consent a subset of 250 consecutive women at delivery, for a further visit and blood collection at 3 months post partum.

50 non-pregnant controls will also be recruited from communities from which participating women are drawn.

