These samples will provide adequate blood for the preparation of thin/thick blood smears, direct measurement of haemoglobin (enrolment and delivery only), DNA extraction for parasite and host genetic typing as well as provide peripheral blood mononuclear cells (PBMC’s) and parasites for in-depth immunology studies. The sample will be collected in heparinized tubes and separated into red cell, white cell and serum fractions. Samples of these fractions may be stored frozen for later laboratory analyses.

1. **Preparation of Blood Smears**

The preparation of thin and thick blood smears will be in accordance with the procedures set forth in the Field and Laboratory Procedures Manual.

1. **Determining Haemoglobin Concentration**

At enrolment and delivery, haemoglobin concentration will be determined directly in the field by using a HemoCue® device (HemoCue, Ångholm, Sweden) and will be expressed as grams of haemoglobin per decilitre. The instrument records haemoglobin concentrations to the nearest tenth of a gram per decilitre.

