## Sample Size Considerations

The primary objective of the study is to determine the effect of IPTp with SP/AZ compared to SP/CQ clearance treatment on prevalence of low birth weight (LBW) in women using ITNs. The overall power and sample size calculations are thus based on this outcome.

The analyses for this primary outcome measure will use Poisson regression (with or without random effects). Sample size calculations for these types of analyses are non-trivial and often require extensive simulations. For that reason we are using an approximate sample size calculation based on comparison of two Poisson rates.

**Table 3**: Sample size calculations for principal outcomes using appropriate two sided tests, a significance level of 5% and a power of 80%.

|  |  |  |  |  |
| --- | --- | --- | --- | --- |
| **End points** | **Expected Outcomes** | |  | **Sample Size** |
|  | Control | AZ-SP |  |  |
|  |  |  |  |  |
|  |  |  |  |  |
| **Primary** |  |  |  |  |
| Prevalence of LBW | 12% | 8.4% |  | 1163 |
| Mean birth weight | 2.94kg | 3.01kg |  | 970 |
|  |  |  |  |  |
| **Secondary** |  |  |  |  |
| Prevalence of *P. falciparum* at delivery (peripheral & placental) by PCR | 30% | 20% |  | 389 |
| Prevalence of malaria in placental histology | 30% | 20% |  | 389 |
| Mean Hemoglobin at delivery | 10.0 | 10.3 |  | 845 |
| Prevalence of bacterial STI at 2nd/final treatment time point | 30% | 10% |  | 72 |
|  |  |  |  |  |

Previous studies suggest that IPTp with SP can increase birth weight by approximately 130 g. ITNs increase birth weight by around 60 g. The effect of adding SP to ITNs is not clear, but we assume that it increases mean birth weight by approximately 70 g. LBW is seen in 16% of babies born to women not using ITNs in PNG. If ITNs decrease LBW by 25% then we will expect 12% of babies to be LBW. SP+AZ may have additional benefits (through control of STIs which impair fetal growth) over SP alone. Our conservative estimate is that SP + AZ will decrease LBW prevalence by 30%. Based on these assumptions, a sample size of 1,163 and 970 women per arm, respectively, are required to find a 30% reduction in LBW and a 70g increase in birth weight with a power of 80% (Table 3).

Assuming, a loss of 20% during follow-up, we will thus enroll 1396 women per arm.

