Assuming that 40% of women have malaria on histology and that the introduction of ITN will decrease this by 25%, we expect a prevalence of malaria on histology of 30%. Based on this assumption and an expectation to collect a good quality placental specimen from 60% of all enrolled women, the chosen sample size is sufficient to detect a 29% reduction in prevalence of malaria histology in women receiving IPTp AZ-SP with a power of 80%(two sided test). This sample size will also be sufficient to detect a 22% reduction in *P. falciparum* prevalence at delivery, a reduction in prevalence of STIs from 25% to 20% and/or a 0.26g/dl increase in maternal Hb with a power of 80%.

An interim analysis will be performed when 1400 women enrolled in the study have delivered and had birth weights recorded. Analysis will compare percentage LBW between control and intervention groups.

Sample size calculations were done [STATA](../STATA) 8 software (College Station, TX)

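### Haemoglobin at delivery is compared without using the enrolment value the trial already collects, and no model names gravidity; the cost is some precision, not validity or adequate power

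*Combined protocol and SAP*

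**What the plan says.** **Haemoglobin.** The whole analysis statement in section 11.4.2 is "Mean haemoglobin levels will be compared using ANOVA". No covariates are named there for haemoglobin, parasite prevalence or STIs. Section 11.4.1 is different: it adjusts the birth-weight ANOVA for the covariates listed for low birth weight (LBW).

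**Baseline value.** Section 6.2.3 states: "At enrolment and delivery, haemoglobin concentration will be determined directly in the field". Section 6.1.4 also lists haemoglobin among the enrolment-visit measurements. Section 15.3, which lists the data to be collected, mentions haemoglobin at delivery only.

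**Gravidity.** It is assessed at enrolment (6.1.4). Section 5.1 says of multigravid women that "the latter will be enrolled in a 1:1 ratio with primigravid women". The background says "The risk of malaria is highest in first pregnancy". Section 6.3.1 produces separate randomisation lists for each health facility, so site is the only stratum. The covariates in 11.4.1 run from infant sex and gestation to "season of delivery (wet vs dry) and site". They are introduced as examples, and gravidity is not among them.

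**Sample size.** Table 3 (section 11.2) specifies "appropriate two sided tests, a significance level of 5% and a power of 80" per cent. Its haemoglobin row reads "Mean Hemoglobin at delivery | 10.0 | 10.3", with 845 women per arm. The text after the table says the chosen size can also detect a "0.26g/dl increase in maternal Hb with a power of 80" per cent.

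**The concern.** A baseline measurement of the outcome is often the most useful covariate a trial has for a continuous endpoint. Here it is taken in the field in both arms before treatment and then left out of the comparison. The haemoglobin analysis also omits site, the one factor on which randomisation is stratified.

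Gravidity is a second pre-randomisation factor that the trial itself treats as important: it limits the number of multigravid women by quota and describes first pregnancy as the period of highest malaria risk. It is not a stratum and is not named as a covariate, so any chance imbalance between arms stays in the estimate unless someone decides to adjust later. An open-ended list leaves that decision to be made after the data are seen.

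At stake are the width of the haemoglobin and birth-weight intervals, and whether the adjustment set is fixed in advance.

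**Working it through.** **Inputs from the documents.** Difference 0.3 g/dl, 845 per arm, two-sided 5%, 80% power, 1163 evaluable and 1396 enrolled per arm, 20% loss (section 11.2). Retained per arm: 0.80 × 1396 = 1117. I use 1117 and 1163 as the range, and assume that every retained woman has a delivery haemoglobin.

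**Assumed, because not in the documents.** Correlation r between enrolment and delivery haemoglobin, 0.3 to 0.5. Mean birth weights by gravidity of 2.80, 2.97 and 3.04 kg in a 2:3:2 mix.

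**1. Reproduce the plan's figures.** No haemoglobin SD is given. For two means, n = 2(kσ/δ)² with k = 1.960 + 0.842 = 2.802. Solving 845 = 2(2.802σ/0.3)² gives σ = 2.20 g/dl; SD 2.2 returns 845, while 2.1 and 2.3 return 770 and 923. As a cross-check, the detectable difference kσ√(2/n) is 0.261 g/dl at 1117 and 0.256 at 1163. Both round to the stated 0.26. The plan's figures are therefore those of an unadjusted comparison.

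**2. Unadjusted power.** For 0.3 g/dl with SD 2.2, power is 89.7% at 1117 per arm and 90.8% at 1163.

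**3. Adjust for enrolment haemoglobin.** The residual SD becomes 2.2√(1 − r²).

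| r | variance removed | n per arm for 0.3 g/dl | detectable difference at 1117 | at 1163 |
|---|---|---|---|---|
| 0 | 0% | 845 | 0.261 | 0.256 |
| 0.3 | 9% | 769 | 0.249 | 0.244 |
| 0.4 | 16% | 710 | 0.239 | 0.234 |
| 0.5 | 25% | 634 | 0.226 | 0.221 |

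Put another way, 1117 women per arm give the precision of 1117/(1 − r²), that is 1227 at r = 0.3 and 1489 at r = 0.5.

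**4. Chance imbalance.** If the enrolment SD is also 2.2, a baseline difference at its 95% limit is 1.96 × 2.2 × √(2/1163) = 0.18 g/dl. Unadjusted, r times that passes into the estimate: 0.05 g/dl at r = 0.3 and 0.09 at r = 0.5, or 18 to 30% of the 0.3 g/dl target.

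**5. Gravidity and birth weight.** The assumed means have a weighted average of 2.941 kg and a between-group variance of 0.0088 kg². Table 3's 970 per arm for 70 g implies an SD of 0.55 kg, so R² = 0.0088/0.3025 = 2.9%. A normal distribution with mean 2.94 kg and 12% below 2.5 kg would need an SD of 0.44/1.175 = 0.374 kg; with 0.375, R² = 0.0088/0.1406 = 6.3%. The range is about 3 to 6%, and the lower figure is the one consistent with the birth-weight row.

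**6. Gravidity and LBW.** With the same means, 4,000 simulated trials (LBW 11.8% against 8.3%) gave power of 79.5% without gravidity and 80.7% with it. At 1117 per arm, the standard error of the log odds ratio rises slightly, from 0.142 to 0.144. Power rises because the conditional odds ratio lies a little further from 1, not because the interval narrows.

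**The case against.** **The list in 11.4.1 is open.** A reader might infer that gravidity is excluded from every model. The text does not say so: the covariates are given as examples, and gravidity could be added. That stands. It does not remove the point, because a list that can be extended later is not a pre-specified one, and 11.4.2 has no list at all.

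**Little is at risk.** A reader might also infer that the haemoglobin comparison is biased or underpowered. Neither follows. Randomisation keeps the unadjusted estimate unbiased, its standard error already allows for chance imbalance, and power for the planned difference is close to 90% or above. The gain is 0.01 to 0.03 g/dl in detectable difference on a device that reads to 0.1 g/dl, and it depends on the assumed correlation; at r = 0.2 the figure at 1117 per arm moves only from 0.261 to 0.256. All of this stands, and limits the weight of the point.

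**Intervals for the binary endpoints.** It is tempting to say that baseline adjustment would tighten every secondary comparison. For LBW, parasite prevalence and STIs the planned model is logistic, and step 6 shows the standard error rising slightly. The precision argument applies to haemoglobin and birth weight only.

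**Going further.** One could ask for the enrolment swab in the STI model and a treatment-by-gravidity interaction. The documents do not support either. Enrolment swabs are collected only when possible (6.1.4), so many values may be missing. Under 6.1.8, treatment after a positive swab differs by arm, so a single common baseline term may predict poorly. No stated objective or power calculation underlies the interaction.

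**Conclusion.** The point holds in a limited form. The plan leaves a baseline measurement out of the haemoglobin comparison and does not name a prognostic factor that the trial itself controls at entry. The consequence is lost precision and uncorrected chance imbalance; nothing here threatens validity, and haemoglobin is adequately powered as planned.

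Most of the benefit comes from enrolment haemoglobin. Its size rests on r between 0.3 and 0.5, which the documents do not give, and on the back-solved SD of 2.2 g/dl. The gravidity benefit is small and rests on assumed group means. Its main value is that naming the factor settles the adjustment before unblinding. This is a worthwhile, low-cost refinement rather than a defect that would change the trial's conclusions.

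**What to change.** - **Section 11.4.2:** replace ANOVA for haemoglobin with ANCOVA on enrolment haemoglobin, with site and gravidity group as covariates.
- **Section 11.4.1:** name gravidity group (primigravid, secundigravid, multigravid) as a fixed baseline covariate for birth weight and LBW, and state that the LBW odds ratio is conditional on the covariates.
- **Section 15.3:** add enrolment haemoglobin to the data list, so that it agrees with 6.1.4 and 6.2.3.
- State how missing enrolment haemoglobin will be handled. Few values should be missing, since section 5.2 uses haemoglobin when screening for exclusion.

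No new visit, sample or participant is needed. The cost is a few lines of text and the handling of those missing values. The change should be made before treatment allocation is revealed for analysis.
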